### Analytic Plan

A description of recruitment will be reported, including the number of participants who are recruited, pass screening, are randomized, complete weeks 1-3, enter week 4, complete the trial (ie, weeks 1-6), and complete the 6-month follow-up.

We will use descriptive statistics to characterize the distribution of demographic variables, tobacco use history (ie, cigarettes per day, use of other tobacco products, and menthol cigarette preference), and CO at baseline. We will examine the aforementioned demographic variables and tobacco use history variables among responders and nonresponders for potential imbalance. If such imbalance is discovered, respective variables will be adjusted in the analysis as covariates.

The analysis will be conducted on an intention-to-treat basis. Primary outcome variables include a binary (yes or no) variable indicating at least 50% reduction in CO readings from baseline and a numeric variable for expired-air CO. For individuals who drop out of the study prematurely, they will be assumed not achieving at least 50% reduction in CO readings, and their numeric CO reading variable after those last reported will be replaced with their baseline CO readings.

To compare incidence proportions of at least 50% reduction in CO readings between study groups at each time point (week 3 or week 6, depending on the objective), generalized linear regression models with a log link will be used to generate incidence ratios and their 95% CIs. To compare numeric CO readings between study groups at each time point (week 3 or week 6, depending on the objective), linear regression will be used to compare group-level differences in CO readings and their 95% CIs when adjusting for baseline CO reading. We chose to use linear regression adjusting for baseline CO reading over ANOVA for change in CO readings from baseline because the adjustment approach properly corrects for “regression to the mean,” provides greater statistical power, and produces unbiased estimates [23-25].

Similarly, we will use generalized linear regression with a log link for binary secondary outcomes (ie, at least 50% reduction in cigarette consumption based on self-report and CO-verified smoking abstinence). Generalized estimating equations will be used to analyze cigarette consumption based on the daily diary, with cigarette consumption at baseline as a covariate. Specific comparisons are as follows: (1) for objective 1, comparison will be made between (a) Group I and combined Groups II at Week 3 and (b) Group I and Group IIa at Week 6; (2) for objective 2, comparison will be made between Group IIa and Group IIb at week 6 among nonresponders at week 3; (3) for objective 3, comparison will be made between Group IIa and Group IIb at Week 6 among responders at week 3; and (4) for objective 4, comparison will be made between Group I and Group IIb at week 6.

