**Figure 1 figure1:**
[figure not shown]
Depiction of study design. Responders are participants who have a ≥50% reduction in cigarette consumption at week 3 (relative to baseline assessment); nonresponders are participants who have a <50% reduction in cigarette consumption at week 3 (relative to baseline assessment). R: random assignment.

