#### Randomization

Approximately 400 participants will be recruited over an approximately 7-month period. After confirming eligibility and obtaining informed consent, participants will be randomized into 3 groups varying only by the availability of research product flavors. Group I (n=150) will have access to the complete flavor profile of the research products (ie, Berry, Citrus, Cinnamon, Wintergreen, Mint, Coffee, and Original). Group IIa (n=125) will have access to only the Original variety for the entire 6-week trial period. Group IIb (n=125) will have access to only the Original variety for the first 3-week period and will be provided access to the complete flavor profile for the second 3-week period. We chose to randomize participants to these 3 groups at study onset rather than have sequential randomizations (ie, first randomize to the full flavor profile or Original-only arm, then rerandomize those in the Original-only arm to either the full flavor profile or remain with the Original-only arm) to simplify the logistics of randomization.

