### Outcome Measures

Primary outcomes of this study are (1) at least 50% reduction in expired-air CO readings from baseline (yes or no) and (2) expired-air CO as a continuous variable (averaged across the week of interest).

Secondary outcomes include (1) at least 50% reduction in self-reported cigarette consumption from baseline (yes or no), (2) CO-verified smoking abstinence (ie, self-reporting no cigarettes smoked in past 7 days and CO<6ppm [22]), and (3) self-reported number of cigarettes smoked (averaged across the week of interest).

Participants who meet the ≥50% cigarette reduction (based on self-reported cigarette consumption) threshold will be identified as “Responders”; those unable to meet this threshold will be identified as “non-Responders.”

We chose to use expired-air CO values in primary outcomes because it is an objective measure not susceptible to recall bias, demand characteristics, or prevarication. Further, expired-air CO closely reflects actual smoke exposure and would not lead to an erroneous conclusion of reduced exposure that results from more intensive smoking of fewer cigarettes as compared to self-reported cigarette consumption. Nonetheless, expired-air CO measures are not without limitation. Factors other than cigarette smoking, such as exposure to environmental pollutants, second-hand smoke, vehicle exhaust, etc, can contribute to elevated expired-air CO, and vigorous exercise can lead to lower expired-air CO. In this study, we include both expired-air CO (taken twice a week) and self-reported cigarette consumption (daily) to provide robust assessments of smoking behavior.

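### Adjustment covariates are chosen by imbalance across a week-3 outcome split that no objective compares, so the adjusted binary primary model is settled only after outcome data are in

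*Protocol article*

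**What the plan says.** The Analytic Plan first describes demographics, tobacco use history (cigarettes per day, other tobacco products, menthol preference) and baseline CO. It then gives a covariate rule in two sentences: "We will examine the aforementioned demographic variables and tobacco use history variables among responders and nonresponders for potential imbalance", and "If such imbalance is discovered, respective variables will be adjusted in the analysis as covariates". It names no treatment groups and no criterion for imbalance, and it does not limit the rule to any objective.

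The legend to Figure 1 defines the split: "Responders are participants who have a ≥50% reduction in cigarette consumption at week 3 (relative to baseline assessment". Under Outcome Measures the same quantity is the first secondary outcome: "at least 50% reduction in self-reported cigarette consumption from baseline (yes or no". All three groups are formed before that point; the Randomization section states: "We chose to randomize participants to these 3 groups at study onset rather than have sequential randomizations".

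The planned contrasts, numbered as in the Analytic Plan, are:

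- Objective 1 has two parts: "comparison will be made between (a) Group I and combined Groups II at Week 3 and (b) Group I and Group IIa at Week 6".
- Objective 2: "comparison will be made between Group IIa and Group IIb at week 6 among nonresponders at week 3".
- Objective 3: the same two groups among week-3 responders.
- Objective 4: "comparison will be made between Group I and Group IIb at week 6".

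Only two covariates are fixed outright: baseline CO in the linear model for numeric CO, and baseline cigarette consumption in the estimating-equation model for diary data. The log-link models, including the one for the binary primary outcome, have none.

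**The concern.** A difference in a baseline variable between responders and nonresponders shows that the variable predicts response. It does not show that the groups being compared differ. The screen therefore answers a question that none of the four objectives asks, and it does so with a variable that is itself a trial outcome.

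The practical consequence is that nobody can write down the adjusted binary primary model until week-3 outcomes have been tabulated. The trial is open-label and the plan states no flagging criterion, so the choice of covariates is left to judgement made with outcome data in view. What is at stake is the pre-specification of the model for the outcome on which the sample size rests.

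**Working it through.** **1. The plan's own figures.** The Power section gives 136 and 64 per arm for objective 1. With a one-sided α of 0.05, power 0.80, pooled variance under the null and no continuity correction,

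n = [1.645·√(2p̄(1−p̄)) + 0.842·√(p₁(1−p₁)+p₂(1−p₂))]² / (p₁−p₂)².

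- 60% v 45%: [1.645·√0.49875 + 0.842·√0.4875]² / 0.0225 ≈ 136.
- 80% v 60%: [1.645·√0.42 + 0.842·√0.40]² / 0.04 ≈ 64.

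The same formula gives the stated 48 and 39 for objectives 2 and 3. No covariate enters any of these, so the point leaves every sample size unchanged.

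**2. The rule set against the contrasts.** The last two columns are two readings of the rule.

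| Objective | Groups compared | Reading A: responders v nonresponders | Reading B: IIa v IIb within stratum |
|---|---|---|---|
| 1 | I v II (week 3); I v IIa (week 6) | not this contrast | not this contrast |
| 2 | IIa v IIb, nonresponders | not this contrast | matches |
| 3 | IIa v IIb, responders | not this contrast | matches |
| 4 | I v IIb | not this contrast | not this contrast |

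Both readings need week-3 responder status before any covariate can be chosen. Neither addresses objectives 1 and 4.

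**3. How often chance alone would flag something.** The document gives no criterion, so a 5% test is assumed, with independent variables. Table 1 and the Analytic Plan suggest about seven candidates: sex, age, race or ethnicity, education, cigarettes per day, other tobacco use and menthol preference. Then 1 − 0.95⁷ = 0.30. For five to eight candidates the range is 1 − 0.95⁵ = 0.23 to 1 − 0.95⁸ = 0.34. This is a null rate. It suits reading B, where randomization makes the null true. Under reading A many candidates would be expected to differ because they are prognostic.

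**4. Chance imbalance inside the strata.** From the Power section, 125 × 0.55 = 68.75 nonresponders and 125 × 0.45 = 56.25 responders per group. The standard error of a between-group difference, in SD units, is √(2/68.75) = 0.171 and √(2/56.25) = 0.189. The 95% chance ranges are ±1.96 × 0.171 = ±0.33 SD and ±1.96 × 0.189 = ±0.37 SD. Sizeable chance imbalances are therefore normal there, and reading A would not look at them.

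**5. Does the screen distort the result?** Reading A was simulated with 4,000 trials per setting, 150 v 250 participants, and a linear model with a baseline covariate. There were six candidates, two of them prognostic, flagged at p<0.05. The number of candidates, their strengths and the flagging rule are assumptions.

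| | With screen | Baseline only |
|---|---|---|
| One-sided type I error | 0.049 | 0.052 |
| Mean estimate (true 0.30) | 0.299 | 0.300 |
| Power | 0.815 | 0.791 |

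The screen added at least one covariate in 99% of trials, 2.0 on average, so it behaves as a selector of outcome predictors. The fitted model varies with the data, but error rate and bias hardly move.

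**The case against.** Several points on the other side stand.

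- **The kinder reading is plausible.** In its list of comparisons the same section uses the word among to mean within a stratum. On that usage the screen checks the right contrast for objectives 2 and 3. It does not change the timing, and it does not reach objectives 1 and 4.
- **Responder status is a reasonable stratifier for IIa v IIb.** Both groups receive the same product through week 3, so product provision cannot separate them before the split. Assignment at onset, known to participants, leaves some room for anticipation, but the document gives no evidence of it. The post-randomization objection weighs mainly on objectives 1 and 4.
- **A statistical analysis plan may hold the threshold and the covariate list.** Their absence is not the complaint. The complaint is the rule that the article does state.

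Three stronger inferences are tempting, and the document does not support them.

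- **That estimates are biased or type I error is inflated.** The candidates are baseline variables, so adjusting for them is not itself a bias, and the simulation found nothing material. It covers a linear model only, so carrying this over to the log-link model is a judgement.
- **That the primary analysis as a whole is open.** Outcomes, time points, contrasts, model families, dropout handling and, for numeric CO, the baseline covariate are all fixed. Only the additional covariates are not.
- **That objective 1 is harmed by having no balance check between its arms.** Randomization already makes those arms comparable in expectation, and observed imbalance should not drive adjustment there either.

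**Conclusion.** The point holds as a matter of pre-specification. On either reading the covariate set is known only after week-3 data are seen, and the rule does not address the contrasts of objectives 1 and 4. On the plainer reading, since no treatment groups are named, it examines a comparison that no objective makes. It matters most for the binary primary outcome, because this screen is the only covariate rule stated for its model.

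The size is modest. No sample size changes, and any effect on bias or type I error is probably small. The 30% chance-flag figure is illustrative, resting on seven independent candidates and a 5% criterion that the document does not give. The case for change is that the remedy is cheap, fixes the models in advance and may gain some precision.

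**What to change.** Delete the two sentences that make adjustment depend on imbalance. Replace them with one short covariate set for all models, named before data lock and chosen without reference to week-3 outcomes. An example is baseline CO, baseline cigarettes per day and menthol preference, all of which the study already collects. The timing matters because the Results section reports 314 participants enrolled by May 2024, so outcome data were already accruing.

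State a fallback for a log-link model that does not converge, for example modified Poisson regression with robust variance. Show baseline tables by randomized group, overall and within each week-3 stratum, for description only and with no consequence for the model.

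The cost is a two-sentence replacement and a little more analysis work; no new data are needed. The one technical downside is a convergence risk for adjusted log-link models in the smaller strata. About 56 responders per group are expected, with assumed week-6 proportions of up to 85%. Keeping the set short and stating the fallback limits that risk.

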#### Baseline Assessment

After randomization and prior to week 1, participants will be asked to track their daily cigarette consumption via a web-based daily diary and provide ≥2 biometrically verified expired-air CO readings via Bluetooth-enabled remote CO monitor (iCOquit Smokerlyzer, Bedfont Scientific) over a period of 3-7 days. These initial data will serve as baseline cigarette consumption and CO for subsequent comparisons.

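### The numeric CO model adjusts for baseline CO, but the model for the co-primary ≥50% CO reduction names no baseline term; the crude ratio is valid, but precision may be lost

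*Protocol article*

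**What the plan says.** Under Outcome Measures, the first primary outcome is "at least 50% reduction in expired-air CO readings from baseline (yes or no"; the second is expired-air CO as a number. The Analytic Plan gives each its own model:

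- Binary CO outcome: "generalized linear regression models with a log link will be used to generate incidence ratios and their 95% CIs". No covariate is named.
- Numeric CO: "linear regression will be used to compare group-level differences in CO readings and their 95% CIs when adjusting for baseline CO reading". This is preferred to an analysis of change because "the adjustment approach properly corrects for “regression to the mean,” provides greater statistical power, and produces unbiased estimates".

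The secondary outcomes follow the same pattern. For the binary ones, "Similarly, we will use generalized linear regression with a log link for binary secondary outcomes", again with no covariate named. For the diary counts, "Generalized estimating equations will be used to analyze cigarette consumption based on the daily diary, with cigarette consumption at baseline as a covariate".

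There is one other route to adjustment: "We will examine the aforementioned demographic variables and tobacco use history variables among responders and nonresponders for potential imbalance", with adjustment if imbalance is found. Tobacco use history is defined there to include cigarettes per day. Baseline CO appears as a separate item in the preceding sentence and is not in the list to be checked. Under Baseline Assessment, baseline CO rests on "≥2 biometrically verified expired-air CO readings" over 3 to 7 days.

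**The concern.** A yes/no variable for a fall of at least half from baseline is a change score cut at a threshold. If baseline is measured with noise, people whose baseline is high by chance tend to cross the threshold more easily, and those with a low baseline less easily. This is the regression to the mean that the plan cites as a reason to put baseline into the numeric model. The plan therefore declines to analyze unadjusted change for one co-primary outcome and, as written, analyzes a thresholded version of it unadjusted for the other.

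The conditional check does not close the gap. It omits baseline CO, and it compares responders with nonresponders rather than the randomized arms, so it is not designed to detect a between-arm difference at baseline.

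At stake is the precision of the outcome that drove the sample size.

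**Working it through.** **1. Reproduce the plan's sample size (Power section).** Inputs: one-sided α 0.05 (z = 1.645), power 0.80 (z = 0.842), 60% vs 45% at week 3, 80% vs 60% at week 6. For an unadjusted comparison of two proportions,

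n per arm = [1.645·√(2p̄(1−p̄)) + 0.842·√(p₁q₁ + p₂q₂)]² / (p₁ − p₂)².

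- Week 3: p̄ = 0.525; [1.645·√0.49875 + 0.842·√0.4875]² / 0.15² = 136. Stated: 136.
- Week 6: p̄ = 0.70; [1.645·√0.42 + 0.842·√0.40]² / 0.20² = 64. Stated: 64.

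The same formula returns the stated 48 and 39 for objectives 2 and 3. The sample size is thus consistent with an unadjusted analysis and is not in error. With 150 vs 250 at week 3, unadjusted power is 89.9%.

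**2. What adjustment would change.** The protocol does not give the spread of log CO or the correlation between baseline and follow-up, so both are assumed. Simulation: 150 vs 250 participants, 60% vs 45%, 1,000 runs per scenario, bivariate normal log CO, baseline SD 0.5, response when follow-up CO is at most half of baseline. The adjusted ratio comes from logistic regression standardized to a risk ratio.

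| Follow-up SD (assumed) | Correlation (assumed) | Correlation of log change with baseline | Variance of log ratio, adjusted ÷ unadjusted |
|---|---|---|---|
| 0.5 | 0.2 | −0.63 | 0.73 |
| 0.5 | 0.3 | −0.59 | 0.77 |
| 0.5 | 0.5 | −0.50 | 0.85 |
| 0.5 | 0.7 | −0.39 | 0.89 |
| 0.8 | 0.2 | −0.40 | 0.93 |
| 0.8 | 0.3 | −0.32 | 0.94 |
| 0.8 | 0.5 | −0.14 | 1.00 |
| 0.8 | 0.7 | +0.10 | 1.01 |

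On the sample-size scale the best case is 136 × 0.73 ≈ 99 per arm and the worst is 136, that is, no gain. Simulated power is 89–92% unadjusted and 90–97% adjusted. Modified Poisson gains slightly less: in the first row the empirical SD is 0.0828 against 0.0924 unadjusted, and (0.0828/0.0924)² = 0.80. With 15% dropout counted as failure, the range of variance ratios narrows to about 0.78–1.02.

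**3. Validity of the unadjusted ratio.** The true log ratio is ln(0.60/0.45) = 0.288. The unadjusted mean across scenarios is 0.286–0.290. With equal rates, the unadjusted test rejects in 4.7–4.9% of runs at a nominal 5%.

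**4. Size of a chance imbalance.** A baseline difference of one standard error moves the unadjusted log ratio by about 0 to 0.05. The standard error of that log ratio is √(0.40/(150×0.60) + 0.55/(250×0.45)) = √(0.00444 + 0.00489) = 0.097. The shift is at most about half of a standard error, and the unadjusted confidence interval already allows for it.

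**5. Week-3 strata.** With 125 × 0.55 ≈ 69 nonresponders per group and 45% vs 70%, a simulation under assumed CO distributions gave a gain of only 1–6% of variance. A log-binomial model with continuous baseline CO failed to converge or reached the boundary in 50–89% of those runs.

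**The case against.** The text never says that the binary model is unadjusted. It gives family, link and effect measure, and a covariate list is commonly left to an analysis plan that is not shown. That stands in part: such a plan could contain the term. But this article does name covariates, for both continuous outcomes and for neither binary model, and it argues for the choice. The inconsistency is in what is written.

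A crude ratio in a randomized comparison is sound, and it matches the power calculation. This stands in full. A reader might infer that the omission biases the incidence ratio or inflates type I error; step 3 shows neither. A reader might also infer that the two co-primary outcomes could disagree for this reason alone; nothing in the documents or the calculations shows that.

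The gain rests on assumed figures and can be nil. This also stands. When follow-up CO is more variable than baseline and the correlation is 0.5 or higher, adjustment buys nothing, and in one scenario the relation between baseline and reduction reverses.

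It is tempting to say that all binary secondary outcomes share the gap. They do not. Cigarettes per day is already in the conditional check, so for ≥50% cigarette reduction the fault is only that adjustment depends on a responder-versus-nonresponder comparison. CO-verified abstinence is defined by absolute criteria, not by change from baseline, so the regression-to-the-mean argument does not reach it.

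**Conclusion.** The point holds as an internal inconsistency and an avoidable loss of precision, not as an invalid analysis. The plan gives regression to the mean and power as reasons to adjust one co-primary outcome for baseline CO, and names no such term for the other, which depends on the same baseline. Adjustment would lower the variance of the log incidence ratio by nil to about a quarter, less when dropouts count as failures and probably little in the week-3 strata. These sizes rest on an assumed baseline log-CO SD of 0.5, follow-up SD of 0.5 or 0.8, and correlations of 0.2–0.7; the protocol gives none of them. The stated sample sizes are unaffected. Correcting this is a worthwhile improvement and not a condition for a valid result.

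**What to change.** Prespecify the following:

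- Baseline CO as a covariate in every model for the ≥50% CO-reduction outcome.
- Baseline cigarettes per day as an unconditional covariate in the ≥50% cigarette-reduction model.
- Estimation of the incidence ratio by modified Poisson regression with robust standard errors, or by logistic regression standardized to a risk ratio. A log-binomial fit with a continuous covariate may not converge at the planned incidences of 60–85%.
- For CO-verified abstinence, baseline adjustment only as an option, justified on prognostic grounds.

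The unadjusted ratio can be kept as a sensitivity analysis. The covariates are already collected and neither design nor sample size changes, so the cost is a few lines in the analysis plan. Because the trial is open-label and had enrolled 314 of about 400 participants by May 2024, the change should be dated and recorded before outcomes are compared by group.

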At the baseline telehealth session, participants will be further assessed for eligibility with additional inclusion or exclusion criteria, including a biometrically verified expired-air CO reading. If eligible, they will be randomized to Group I or Group IIa/IIb. During the 3- to 7-day baseline assessment period, participants will provide CO readings every other day and record their cigarette consumption in web-based daily diary survey. Upon the completion of the baseline assessment period, participants will begin week 1 when they receive the research product to use in their natural environment, following group configurations shown in Figure 1. During weeks 1-6, participants will respond to daily diary surveys to report their use of the research product (by flavor, if applicable), cigarette consumption, and use of other tobacco products. They will request and receive research products weekly. They will also be alerted to provide pseudorandom biometrically verified CO readings once every 3 days. At the end of week 3, female participants of childbearing potential will be asked to provide urine pregnancy test results; those with positive results (ie, pregnant) will be discontinued from the study and referred to their primary care provider. Six months after the study ends, participants will be recontacted to complete a follow-up survey with questions related to tobacco-use behaviors (including cigarette smoking and *on!* NP use), reasons to use or not use *on!* NPs, risk perceptions of use of a variety of tobacco products at the category level (eg, cigarettes, smokeless tobacco, and NPs), and respiratory symptoms. The main purpose of the 6-month follow-up survey is to collect information on participants’ posttrial tobacco use behaviors when they are no longer provided with *on!* NPs. None of our research questions rely on the 6-month follow-up survey.

Participants will be presented with the following debriefing statement at the conclusion of the study (ie, at the end of Week 6) or upon discontinuation of participation (ie, withdrawal from the study):

We would like to emphasize that in conducting this research, we were not trying to market, sell or promote a tobacco or nicotine product to you. Finally, oral tobacco-derived nicotine products should never be viewed as an alternative to quitting all tobacco products.

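### The dropout rules cover only the CO outcomes; the GEE on diary cigarettes has none and can be biased if people leave because of their on-trial smoking

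*Protocol article*

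**What the plan says.** The Analytic Plan sets the frame: "The analysis will be conducted on an intention-to-treat basis". It then says what happens to people who leave early, but only for CO. For the binary outcome, "they will be assumed not achieving at least 50% reduction in CO readings". For the continuous one, "their numeric CO reading variable after those last reported will be replaced with their baseline CO readings".

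The numeric cigarette outcome gets a different method: "Generalized estimating equations will be used to analyze cigarette consumption based on the daily diary", adjusted for baseline consumption. Nothing is said there about missed diary days, dropout, weights, working correlation or time structure. The sentence before it carries the log-link model over to the binary secondary outcomes; it does not carry the CO dropout rule over to the GEE.

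Outcome Measures lists the outcome among the secondary ones, as "self-reported number of cigarettes smoked (averaged across the week of interest". Study Procedure describes the data source: "During weeks 1-6, participants will respond to daily diary surveys to report their use of the research product"; the same diaries record cigarettes. For objective 1 the week-6 comparison is "Group I and Group IIa at Week 6".

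**The concern.** Taken as written, the same person who leaves in week 4 is handled in two ways. For CO they stay in the week-6 comparison at their baseline value. For cigarettes they have no week-6 diary, and the GEE works from the diaries that exist. Outcome Measures presents CO and self-report together as complementary evidence on smoking, yet the two would rest on different missing-data assumptions.

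Ordinary GEE needs dropout to be unrelated to the outcome once the model covariates are accounted for. The only stated covariate besides group is baseline consumption. If people leave because the pouch is not replacing their cigarettes, dropout depends on smoking after baseline, and that is not in the model. Participants know their group, so the tendency may also differ by arm. Where heavier continuing smokers leave more often from the arm that smokes more, the arms look more alike than they are.

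A smaller point is that the outcome is one weekly average per person while the model uses daily records. With an independence working correlation, people who return more diaries count for more.

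**Working it through.** **What the plan gives.** There is no figure for this analysis and no dropout rate, so there is nothing of the plan's own to reproduce. The stated sample sizes for objective 1 (136 and 64 per arm) do reproduce with a 1-sided pooled two-proportion formula, but they concern CO and do not bear on this point.

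**Principle.** GEE solves Σ Dᵢ′Vᵢ⁻¹(Yᵢ − μᵢ) = 0 over the observed records. If dropout depends on earlier on-trial values of Y, the observed residuals no longer average to zero, so the solution can be biased. With a linear model and a working correlation near the truth, the equations come close to those of a normal likelihood and the bias shrinks. With independence and group-by-week terms, earlier weeks lend nothing to week 6.

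**Simulation 1 (all values assumed).** 150 v 125 participants; 200 runs per scenario. Baseline is normal with mean 14 and SD 6, limited to 5–40 cigarettes/day. On-trial mean is 0.6 × baseline, plus a person effect (SD 3), week-level drift and daily noise (SD 2). The Group I effect grows to −2.0 by day 21. Dropout occurs at the end of weeks 1–5. GEE was fitted to weekly means of available diaries with week, group-by-week and baseline terms. Shortfall = 1 − estimate/(−2.0).

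| Dropout depends on | Dropout, I / IIa | GEE, independence | GEE, exchangeable | Return to baseline |
|---|---|---|---|---|
| (a) nothing | 21% / 21% | −1.98 | −2.00 | −1.57 |
| (b) baseline smoking | 22% / 22% | −1.94 | −1.97 | −1.51 |
| (c) on-trial smoking, same rule in both arms | 22% / 31% | −1.64 | −1.90 | −1.85 |
| (d) on-trial smoking in IIa only | 14% / 43% | −0.24 | −1.79 | −2.33 |

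The Monte Carlo standard errors are 0.03–0.04.

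- (a) and (b): no material bias. The largest gap, 0.06 in (b), is under two standard errors (0.06/0.035 = 1.7).
- (c): shortfall 1 − 1.64/2.0 = 18% with independence; 1 − 1.90/2.0 = 5% with exchangeable.
- (d): 1 − 0.24/2.0 = 88% and 1 − 1.79/2.0 = 10.5%.
- In all four, independence GEE matched a week-6 observed-cases regression to two decimals. Exchangeable GEE did not work that way, because the earlier weeks of people who left still contribute.
- Return to baseline is not neutral. Under random dropout the people set to baseline carry no arm difference, so about −2.0 × (1 − 0.207) = −1.59 is expected, against −1.57 found. In (d) it overshoots.

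**Simulation 2 (for the remedy; also assumed).** 400 runs, 150 v 125, log-normal baseline with median 14, week-6 smoking at about 50% v 68% of baseline, dropout depending on the previous week's smoking. The comparator is a baseline-adjusted regression on week-6 observed cases, not a longitudinal GEE.

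| Dropout, flavor / Original | Full data | Week-6 observed cases | Likelihood, all weeks |
|---|---|---|---|
| unrelated to smoking | −2.56 | −2.56 | −2.55 |
| 24% / 28% | −2.48 | −2.25 (9% too small) | −2.44 |
| 29% / 36% | −2.54 | −2.10 (17%) | −2.47 |
| 17% / 37%, stronger in Original | −2.42 | −1.27 (48%) | −2.34 |

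The likelihood estimate stays within about 3% of the full-data value throughout (worst case 1 − 2.344/2.424 = 3.3%).

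**The case against.** The strongest reply is that the article is a condensed protocol. Weights, working correlation and handling of missed diaries for a secondary outcome commonly sit in an analysis plan, which is not shown. That stands as far as it goes: nothing says the GEE is unweighted. But the article itself chose the method and put explicit dropout rules for CO beside it, so what is fixed here is uneven, and the method named needs a stronger missingness assumption than the data require.

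Three stronger readings are tempting, and the document does not support them.

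- *That this is a completers' analysis at odds with intention to treat.* GEE uses every submitted diary, including those of people who later leave. The week-6 contrast reduces to observed cases only under some specifications, such as independence with group-by-week terms or a week-6-only model. Intention to treat settles who is analysed and in which arm; an available-data GEE does not by itself breach it.
- *That the GEE is valid only if dropout is unrelated to smoking.* Dropout may depend on group and baseline smoking, both modelled; scenario (b) shows this.
- *That half the effect would be lost.* The 48% figure needs a week-6 observed-cases regression and assumed arm-specific dropout of 17% v 37%.

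It is also fair that the outcome is the third-listed secondary one, that both primary outcomes have a stated rule, and that participants are paid for each completed daily survey, which works against sporadic gaps. The extra weight given to frequent reporters arises only under independence and was not quantified.

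**Conclusion.** The point holds in a limited form. Dropout handling is stated for CO only, and the cigarette GEE as described is exposed to bias if leaving depends on on-trial smoking. The size cannot be derived from the document. Under the assumed smoking-dependent dropout, the week-6 difference was about 5–10% too small with an exchangeable correlation; with independence, 18% to 88% of it was lost. Under random or baseline-dependent dropout there was no material bias.

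To put the milder case in proportion: in (c) the sampling SD of one trial's exchangeable estimate is about 0.031 × √200 = 0.44, so a bias of 0.10 is under a quarter of it. With independence the bias of 0.36 is about three quarters of 0.034 × √200 = 0.48.

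The direction is not fixed either. Attenuation follows from heavier smokers leaving Group IIa more often; the opposite pattern would exaggerate the effect. This is a worthwhile improvement to a secondary analysis and no threat to the primary CO results.

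**What to change.** Replace the GEE sentence with one of two specifications, applied to weekly mean cigarettes/day, as Outcome Measures defines it, for weeks 1–6 in all randomized participants:

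1. A likelihood-based repeated-measures model with group × week, baseline × week and an unstructured covariance across weeks; or
2. GEE weighted by the inverse probability of still reporting, estimated from group, baseline and prior-week cigarettes.

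Read off the week-3 and week-6 contrasts from it. State how missed days enter a weekly mean and which missingness assumption the analysis rests on. Add the return-to-baseline rule used for CO as a sensitivity analysis only. It makes the cigarette result comparable with the primary outcome, but it missed the true difference in every scenario of simulation 1, so it should not be the main analysis.

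The cost is plan wording and a little programming; the diaries are already part of data collection. The downside is reliance on missing at random, plus a distributional assumption (option 1) or a correct weight model (option 2). Neither option covers dropout driven by smoking that was never recorded.
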